### Recruitment

To achieve adequate enrolment of participants, school recruitment will be conducted which is scheduled to commence on 19 January 2017. Thereafter, the returned consent and assent forms will determine whether the target sample size was achieved. If it has, then no more schools will be recruited.

### Assignment of interventions

#### Allocation: sequence generation, allocation concealment mechanism and implementation

The statistician will generate the computerised allocation sequence. The random allocation ratio will be 1:1 while the randomisation will be stratified into 2:1 where the lower quintile has a higher number of assignments of participants per school when compared to the higher-quintile schools. The written allocation of the assignment of participants will be sealed in an envelope which contains identification numbers. These identification numbers will be distributed across the lower- and higher-quintile schools. A sufficient number of schools will be included to meet the targeted sample size. The researcher will open the envelope to determine the allocation of schools. The stratification of the sample will occur in the following order; mixed-gender schools, schools within quintiles 2 and 3 and 4 and 5 and finally according to the eligibility characteristics and restrictions.

### Blinding

The principal investigator will be fully blinded to the study. The primary researcher will complete the following: obtain permission from the relevant individuals; recruit participants; recruit research assistants; assist research assistants with training of intervention group teachers to use CCR intervention and; observe the administration of the CCR intervention only along with research assistants. A team of research assistants will be utilised to assist with randomisation and blinding of the primary researcher regarding the administration and data capturing of the SROM.

### Data collection, management and statistical analysis

#### Data collection

As mentioned, the SROM will be administered pre intervention and will be administered 6 months post intervention to all participants. Participation retention will be promoted through rigorous planning of arranging data collection at times and dates most convenient for the schools.

#### Data management

The Consolidated Standards of Reporting Trials (CONSORT) Statement will be used when reporting on the trial. Imputation will be included related to the missing data according the cause for missing data such as absenteeism. Raw data will be captured on a Microsoft Excel spreadsheet using allocated coded numbers that will be used during data collection. Control and intervention groups will be captured on two separate spreadsheets and within each group, each quintile will be included. Answers for each question will be included on the spreadsheet using a number between 1 and 5 (strongly disagree = 1, disagree = 2, not sure = 3, agree = 4 and strongly agree = 5). Negative items will be reversed scored (e.g. strongly disagree will be 5). Total SROM mean scores, i.e. global scores, will be calculated at this point. Data will be cross-checked between the research assistants and then rechecked independently by another research assistant to minimise errors. Discrepancies in the data capturing will be reviewed and rechecked and corrections will be made where applicable. According to the Guidelines for Good Practice in the Conduct of Clinical Trials with Human Participants in South Africa, it is recommended that the data be kept for 15 years after the formal discontinuation of the trial [31]. The principal investigator will be responsible for securely storing the data as well as discarding the data.

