### Intervention

The CCR intervention consists of a social story, role-play, and a semi-structured teacher-led discussion. It will be administered by the class teacher and will require active participation of learners. The teacher will be required to read the story to the class. Thereafter, she will select students in her class to perform the role-play. The role-play contains the same story plot of the story that she will have read to the class. This was purposely done in this manner in order to physically put the study’s participants in the characters “shoes”. The teacher-led discussion will include guidelines on which topics should be covered, however, teachers may also explore these topics in greater depth if they would like to.

The CCR intervention will be administered to the intervention groups only. While the CCR intervention is aimed to be largely self-sufficient and user friendly, it is a supported guide and thus teacher training will be required. Training will be required specifically around the discussion activity as teachers may require assistance with targeting the issues around diversity, difference, race and culture in the area of communication and stuttering. Queries and concerns will be addressed as part of the training. Teachers in the intervention groups will be encouraged to answer questions that arise from participants around the CCR intervention, discuss the questions and make notes in a logbook for the researcher.

The CCR intervention will only be administered once, as it is a single-dose intervention tool. The researcher will observe how teachers administer the CCR intervention and take notes during this time. The teacher will be left to administer the CCR intervention as she was trained and without interference from the researcher at this stage. The teacher may provide voluntary feedback at that stage. The teacher will also be given the opportunity to discuss their experiences with the researcher after the 6 months’ post-intervention data is collected.

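### SROM data are captured, scored and corrected in one file per arm, so coded numbers do not mask allocation from the staff handling the outcome, and the Blinding section does not address this

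*Protocol article*

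**What the plan says.** In the Protocol article, Data management sets the file layout: "Control and intervention groups will be captured on two separate spreadsheets and within each group, each quintile will be included". Records carry coded numbers. Item answers are entered as 1 to 5, negative items are reversed, and global scores are computed at that stage. Assistants compare entries, a further assistant rechecks them, and "Discrepancies in the data capturing will be reviewed and rechecked and corrections will be made where applicable". No step hides the arm before scoring or correction. The same section makes the principal investigator responsible for storing and discarding the data.

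The Blinding section makes two claims. One is general: "The principal investigator will be fully blinded to the study". The other is limited: assistants are used for "blinding of the primary researcher regarding the administration and data capturing of the SROM". Among the primary researcher's tasks, that section lists this one: "observe the administration of the CCR intervention only along with research assistants". Another task given to the same role is to "assist research assistants with training of intervention group teachers to use CCR intervention". The section also says the assistants help with randomisation. Data monitoring and auditing again gives capture and audit to research assistants, together with a statistician.

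Two other places bear on who knows the allocation. The Allocation section says "The researcher will open the envelope to determine the allocation of schools", and the Intervention section says "The researcher will observe how teachers administer the CCR intervention and take notes during this time".

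**The concern.** The SROM is the trial's only outcome instrument, and it supplies both the global score and the three subscales. Two risks follow from the stated layout.

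- **Handling with the arm known.** Coded numbers mask a pupil's identity. They do not mask allocation when the file itself separates the arms. Entry, reversal, checking and correction can then all be done with the arm in view.
- **Errors confined to one arm.** In a common file, a faulty reversal or formula hits both arms alike and largely cancels in the comparison. In arm-specific files the same mistake can sit in one arm only and appear as a treatment effect, or hide one.

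The Blinding section does not close this gap. It protects two roles and says nothing about the masking of the assistants to whom SROM work is given.

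**Working it through.** **Reading the sections together**

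- *Primary researcher.* Knows the CCR schools from observing lessons, and also from opening the envelope if the researcher in the Allocation section is this person. The blinding claimed is only for SROM administration and capture.
- *Research assistants.* As a group they help with randomisation, train CCR teachers, observe CCR lessons, and administer, capture and check the SROM. They are nowhere said to be blinded, and no division of these tasks is given.
- *Principal investigator.* Said to be fully blinded, yet responsible for storing data that are split by arm. The two statements are compatible only if the files are not opened, or if storage begins after analysis. The text says neither.
- *Files.* Separated by arm at capture, before reversal, scoring and correction.

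Even if different assistants did the training and the data entry, the split files would still show the arm to those entering and correcting data.

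**Illustration of a coding error in one file**

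The plan gives no figure for this, so there is none to reproduce. Inputs: 20 items scored 1 to 5 (Primary outcomes); planned means 77.91 and 72.66, difference 5.25 (Sample size with power analysis). Assumptions: the global score is the 20-item sum, as means of this size imply, and the affected item has the average score.

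An item correctly scored x becomes 6 − x if not reversed, so the arm mean falls by x − (6 − x) = 2x − 6.

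- Error in the intervention file only: x = 77.91/20 = 3.90; un-reversed 6 − 3.90 = 2.10; shift 1.79 points; 1.79/5.25 = 34%. The planned difference would shrink.
- Error in the control file only: x = 72.66/20 = 3.63; un-reversed 2.37; shift 1.27 points; 1.27/5.25 = 24%. The difference would be inflated.
- Same error in both arms, as in a common file: 1.79 − 1.27 = 0.52 points, about 10% of 5.25, towards zero. If the arms were truly equal, the net error would be nil.

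**Effect of baseline adjustment**

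The 6-month comparison adjusts for baseline. If the same item were miscoded in that arm at baseline too, with a shift of similar size, the residual would be about shift × (1 − b), where b is the baseline slope. The document does not give b. I assume 0.4 to 0.84; the upper end is the reported test-retest reliability, whose interval is not stated.

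- Intervention file: 1.79 × 0.60 = 1.07 down to 1.79 × 0.16 = 0.29 points.
- Control file: 1.27 × 0.60 = 0.76 down to 1.27 × 0.16 = 0.20 points.

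The 24% to 34% range therefore needs an error at follow-up only.

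**The case against.** A reader might infer that the stated blinding simply fails, because the researcher opens the allocation and watches CCR lessons. The text does not support that. The primary researcher's blinding is limited to SROM administration and capture, and the same section openly lists CCR training and observation among that person's tasks. Knowing the allocation does not contradict having no hand in the SROM. The general claim concerns the principal investigator, and nothing ties the envelope or the observation to that role.

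A reader might also infer that the same individuals train, observe and handle the SROM, so that everyone touching outcome data also delivered the intervention. Undivided roles are the natural reading, but the article never says so person by person. A rota could sit in the full protocol.

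Other points also carry weight. Pupils rate themselves on fixed responses with a fixed reversal rule, which leaves capture staff little discretion. Entries are checked twice, and an item un-reversed for a whole arm would have to survive both checks. The article does not say the files are labelled, only that they are separate. And a reversal error is a data-quality fault, so its size does not measure bias from lack of blinding.

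These points limit the likely harm but do not remove the concern. The split by arm is stated affirmatively, so it is not a detail left out for brevity. The described checks include no masking of the arm.

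**Conclusion.** The point holds in a limited form. The plan fixes a layout that reveals the arm during capture, scoring and correction, and that lets a scoring error fall on one arm. The Blinding section leaves the assistants' masking unstated, and it sits awkwardly with the principal investigator's custody of arm-split data. This is a weakness in data handling and in clarity. It does not show that every stated form of blinding fails, and it does not invalidate the design.

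Bias from handling or administering the SROM with the arm known cannot be quantified from the document. The 1.3 to 1.8 points is an illustration of one coding error under the assumptions given above, not a forecast, and it would be wrong to read it as an expected loss of a third of the planned effect. The change is worth making because the risk is avoidable at little cost.

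**What to change.** - Capture all SROM forms in one file, with student and school codes and no arm variable.
- Apply one scoring script, including the reversal of negative items, to all records at both time points.
- Complete checking and correction, lock the data, and only then merge the allocation.
- Where the existing team allows, have the SROM administered and captured by assistants who do not train teachers or observe lessons.
- Reword the Blinding section to state, for the principal investigator, primary researcher, assistants and statistician, who is blinded to what and until when. Reconcile this with the Allocation section and with the storage duty under Data management.

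The cost is a small change in data layout and some rewording. Separating the assistants' roles depends on the size of the team, which the article does not give, so that step may not be free.

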#### Statistical methods

The analysis will follow the intention-to-treat (ITT) principle and will be reported according to CONSORT guidelines [32]. The GEE will be used to compare the groups on global SROM and subscales to address the primary objective. Assuming an exchangeable correlation structure within a school, GEE will allow for possible clustering within a school to be accounted for. The unit of analysis will be the grade-7 student. The results will be reported as estimate of the difference between groups, 95% confidence interval and associated *p* value. All *p* values will be reported to three decimal places with those less than 0.001 reported as *p* < 0.001. The criterion for statistical significance will be set at alpha = 0.05. The subgroup hypothesis will be tested by adding an interaction term of the quintile group (lower versus higher) × intervention (CCR versus usual practice) in the model. Similarly, this analysis will be used to address the secondary objective by analysing the PSD, VI and SP constructs on the SROM. The subgroup analysis will use this method of analysis to address the subgroup analysis between and across the quintiles. See Additional file 1: Table S1 for a summary table of the objectives, outcomes, hypotheses and methods of analysis.

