### Secondary objectives

The secondary objective is to determine the treatment effect on attitudes towards stuttering among Grade 7 participants based on the SROM subscales of PSD, SP and VI.

It is hypothesized that there may be an improvement in each subscale but it is unknown which will show a greater improvement. These subscales will be compared to the control group treatment effect. This study will also evaluate the areas of interaction between peers that exist and may be self-perceived.

The subgroup analysis objective is also to determine the primary objective between and across the lower and higher quintile school clusters. Previous studies have shown that the lower quintile schools are more negative than the higher quintile schools initially [19]. It is hypothesized that both quintiles in the intervention groups will yield positive shifts in treatment effects when compared to the control group while it is unknown which quintile will be most positive, or where the greatest shifts will occur.

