## Methods

### Trial design

This study will make use of a stratified cluster randomised controlled trial with the schools as the unit of randomisation. Using a 1:1 allocation ratio, schools will be stratified into two quintile groups (lower versus higher). The quintiles will be randomised, to receive the CCR intervention or usual practice, to eliminate selection bias and to control for any extraneous variables. This will also allow each lower and higher quintile school an equal opportunity to be included (See Additional file 1: Figure S2).

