### Sample size with power analysis

The sample size calculation was based on previous CCR intervention studies [18, 19, 26]. With the proposed sample size of *n* = 350 students (*k* = 10 schools) in each of the two groups (i.e. assuming a 1:1 allocation ratio), the study will have the power of 80% to yield a statistically significant result using a generalised estimating equations (GEE) model (assuming an intention-to-treat (ITT) principle for the analysis) of the difference between mean in SROM global scores at 6-month adjusting for baseline (pre-intervention) SROM global score at alpha = 0.05. This computation is based on a pilot study [19] which assumes that SROM global scores are normally distributed, the mean difference is 5.25 (corresponding to mean of 77.91 (for the intervention group) versus 72.66 (for the control group)) and the common within-group standard deviation is 11.90 and an ICC (intra-school correlation coefficient) of 72.70.

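### The statistical methods section gives the primary GEE no covariates, although the power rests on baseline adjustment and randomisation is stratified by quintile group; the model should be stated once, with both terms

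*Protocol article*

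**What the plan says.** The protocol article describes the primary analysis, or the design it must respect, in these places.

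- Statistical methods: "The GEE will be used to compare the groups on global SROM and subscales to address the primary objective". The section fixes the working correlation (exchangeable within school), the unit of analysis, alpha and the reporting of p values. It names no covariate. Quintile group appears only as an interaction with intervention, added for the subgroup hypothesis.
- Sample size with power analysis: the 80% power refers to a GEE for the "difference between mean in SROM global scores at 6-month adjusting for baseline (pre-intervention) SROM global score at alpha = 0.05".
- Trial design: "schools will be stratified into two quintile groups (lower versus higher"), with schools as the unit of randomisation.
- Secondary objectives: "Previous studies have shown that the lower quintile schools are more negative than the higher quintile schools initially". By the article's own account, the stratification factor is related to the outcome measure at baseline.

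The SROM is given to all participants before the intervention and at 6 months, so both candidate covariates are already available.

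**The concern.** An analyst who takes the Statistical methods section at its word would fit 6-month SROM on arm alone. Two things would follow.

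First, that is not the model behind the stated power. Pre-intervention score is usually the strongest predictor of the later score. With 20 schools, chance differences between arms in school baselines are also a real possibility, and an arm-only model leaves them uncorrected.

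Second, stratified allocation balances quintile group between arms, so the treatment estimate does not vary with it. An arm-only model nevertheless counts the difference between quintile groups as residual variation between schools. The reported standard error is then larger than the true sampling variability, and the test is conservative.

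Because two sections point to different models, the choice could also be made after the data are seen.

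**Working it through.** **Inputs from the article (sample-size section):** 350 students and 10 schools per arm, so 35 per school; difference 5.25; SD 11.90 (variance 141.61); alpha 0.05, taken as two-sided.

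**Assumptions, because the article does not give a usable value:** ICC 0.05 to 0.30; pre-post correlation r from 0.5 to 0.84, the same at school and pupil level (0.84 is the reported test-retest reliability, used as an optimistic bound); a gap between quintile groups of 0 to 6 points; seven lower and three higher quintile schools per arm.

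**The article's own figure.** The 80% cannot be reproduced, because the printed ICC of 72.70 is not possible for a correlation. Ignoring clustering, 350 per arm gives over 99.9%. Working backwards, 80% corresponds to an ICC of about 0.098 without baseline adjustment, and of about 0.14 (r = 0.5) to 0.40 (r = 0.84) with it. So the power statement depends heavily on whether the model is adjusted.

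**Baseline.** SE² = 2 × 141.61 × (ICC + (1 − ICC)/35)/10. Adjustment multiplies this by (1 − r²). Power = Φ(5.25/SE − 1.96). For ICC 0.15: SE² = 28.322 × (0.15 + 0.02429) = 4.936, SE = 2.222, power 66%. With r = 0.5: SE = 2.222 × √0.75 = 1.924, power 78%.

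| ICC (assumed) | unadjusted | r = 0.5 | r = 0.84 |
|---|---|---|---|
| 0.05 | 94% | 98% | >99% |
| 0.10 | 79% | 89% | >99% |
| 0.15 | 66% | 78% | 99% |
| 0.30 | 41% | 52% | 90% |

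Omitting baseline inflates the variance by 1/(1 − r²): 1.33 at r = 0.5 and 3.40 at r = 0.84.

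**Stratum, with no baseline term.** School means were simulated with equal school sizes and an uncorrected sandwich standard error. The SE ratio is the mean reported SE divided by the actual spread of the estimates.

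| ICC | gap | SE ratio, arm only | type I error, t | type I error, normal | power (t), arm only | power (t), arm + stratum |
|---|---|---|---|---|---|---|
| 0.05 | 3 | 1.03–1.04 | 3–4% | 6% | 88–89% | 92% |
| 0.05 | 6 | 1.24–1.27 | 1% | 2% | 77% | 92% |
| 0.15 | 3 | 0.98–0.99 | 4% | 7% | 58% | 60–61% |
| 0.15 | 6 | 1.10–1.12 | 2–3% | 4% | 47–48% | 59% |

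With the stratum in the model, type I error is about 4% to 5% on the t reference and 8% to 9% on the normal reference. The normal figures are higher because an uncorrected sandwich SE is too small with 20 schools, which is a separate matter.

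**Stratum, once baseline is in.** The largest gain from adding it was at ICC 0.15, gap 6, r = 0.5: power rose from 78.0% to 81.8% (normal) or from 67.9% to 71.4% (t). Elsewhere the change was smaller, and with no gap or a small one it was sometimes slightly negative.

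**A middle case** (ICC 0.098, r = 0.6, 5-point gap, t test). School-mean variance is 141.61 × (0.098 + 0.902/35) = 17.5, and the stratum contributes 0.3 × 0.7 × 5² = 5.25. If the 5.25 is added to the 17.5, arm-only power is about 65%; if it is counted within it, about 78%. Type I error is 2% to 3%. With baseline and quintile, power is about 89% and 96% respectively; quintile supplies under 1 point of that once baseline is in.

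**The case against.** The strongest reply is that the article never says the analysis is unadjusted. The sample-size section describes a baseline-adjusted GEE, and the GEE in Statistical methods can be read as that same model. Adding an interaction to the model is also compatible with quintile already being a main effect. Covariate lists are often left to a SAP, and the section refers to a table of analysis methods in Additional file 1, which is not shown.

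Much of this stands. A reader might infer that the trial has decided against baseline adjustment, but the documents do not support that. What remains is that two sections describing the same analysis differ on a term that changes the power materially, and that the stratification factor is mentioned only for the subgroup test. This is a mismatch in what the article states, not just detail left out.

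A reader might also infer that the planned standard error is simply wrong. That goes too far. Omitting baseline costs precision but does not bias the standard error. Only omitting the stratum misstates it, and only if quintile still predicts the score at 6 months, whereas the article reports a difference initially. The error is in the conservative direction, and with a gap of 3 points or less the SE ratio stayed between 0.94 and 1.04. Baseline SROM would absorb most of a gap already present at the start.

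Finally, a loss of power from about 90% to about 65% might be quoted as the size of the problem. That contrast rests on an assumed ICC, correlation, gap and split, and on adding the gap to the stated variance; counted within it, arm-only power is about 78%. Most of the difference comes from baseline, which the sample-size section already includes.

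**Conclusion.** The point holds as a mismatch that should be resolved. Read literally, Statistical methods gives a less precise primary test than the one the trial was powered on. The loss is a variance factor of 1/(1 − r²): about 10 to 12 percentage points of power at r = 0.5 for ICCs of 0.10 to 0.30, and more at higher r. It cannot be fixed more closely, because r is not given and the printed ICC is unusable.

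If quintile remains prognostic at 6 months and both terms are left out, the test is also conservative: type I error of about 1% to 4% on a t reference for assumed gaps of 3 to 6 points. Such a test does not inflate false positives through this route; it makes a real effect harder to detect. The stratum adds little power once baseline is in the model (at most about 4 points), and the case for it rests mainly on matching the analysis to the randomisation.

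**What to change.** In Statistical methods, state the primary model in full: 6-month global SROM score on arm, baseline global SROM score and quintile stratum (lower or higher), fitted by GEE with schools as clusters and the exchangeable working correlation already chosen. Refer to the same model in the sample-size section, which already has the baseline term. For PSD, SP and VI, use the same model with the matching baseline subscale score. For the subgroup test, add the quintile-by-intervention interaction to this model, so that quintile is a main effect throughout. Check that the table of methods in Additional file 1 and any SAP agree.

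The cost is wording only. Both variables are already collected, and no change to recruitment, randomisation or assessment is needed. It should be done before the 6-month data are examined, so that the covariates are not chosen with the results in view.

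### With 20 schools and no small-sample correction stated, default GEE inference would run the 5% test at about 7-10% for the main effect and 10-13% for the quintile interaction

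*Protocol article*

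**What the plan says.** The Statistical methods section of the protocol article makes the grade-7 student the unit of analysis and handles clustering through the GEE: "Assuming an exchangeable correlation structure within a school, GEE will allow for possible clustering within a school to be accounted for". Results are to be given as group differences with 95% confidence intervals and p values, and "The criterion for statistical significance will be set at alpha = 0.05". The same model serves the global SROM score, the three subscales and, through an added product term, the comparison of lower with higher quintile schools.

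The number of clusters is in Sample size with power analysis: "With the proposed sample size of *n* = 350 students (*k* = 10 schools) in each of the two groups". That makes 20 schools and 700 students, on average 35 per school.

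The article does not name the variance estimator, the reference distribution or any small-sample adjustment. The allocation section mentions a 2:1 stratification favouring the lower quintile, but words it as participants per school. It does not say how many schools fall in each stratum.

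**The concern.** The usual GEE robust (sandwich) variance is justified when the number of clusters is large. With few clusters two things go wrong together. Residuals are too small because the fitted means have been pulled towards the data, so the standard error is biased downward. The normal reference also ignores the uncertainty in a variance estimated from few schools. Adding students per school cures neither.

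If the defaults were used, the primary p value and all the intervals would look more precise than the design allows. The quintile interaction, which answers a named subgroup objective, would suffer most because its variance rests on only a few schools per cell.

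**Working it through.** **Inputs.** From Sample size with power analysis: 10 schools and 350 students per arm, difference 5.25, SD 11.90. From Statistical methods: exchangeable GEE, alpha 0.05 (taken as two-sided, to match the 95% interval). Assumed: lower:higher schools per arm of 5:5, 6:4 or 7:3, the last being nearest to 2:1 if that ratio is read as schools.

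**The plan's own figure.** The article claims 80% power with "the common within-group standard deviation is 11.90 and an ICC (intra-school correlation coefficient) of 72.70". An ICC cannot be 72.70, and reading it as 0.727 gives 21% power. Solving for 80% with a normal test and no baseline gain gives an ICC of about 0.098: design effect 1 + 34 × 0.098 = 4.34; SE = 11.90 × √(2/350 × 4.34) = 1.87; 5.25/1.87 = 2.80. The printed ICC is a separate matter and is used here only as a benchmark for the cost. The error rates below barely change over ICC 0.05 to 0.5.

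**Main effect, arm only, equal school sizes.** The GEE estimate is then a difference of averaged school means. With k schools per arm, the uncorrected sandwich uses SS/k² per arm, where the unbiased form is SS/[k(k−1)].
- Variance ratio = (k−1)/k = 9/10, so the SE is √0.9 = 0.949 of what it should be.
- Rejecting at 1.96 amounts to |t| with 18 df exceeding 1.96 × 0.949 = 1.859, which has probability 7.9%.
- A 400,000-replicate cluster-mean simulation gave 7.9-8.0%. Student-level GEE simulations (with and without a baseline covariate, equal or varying school size) gave 7.0-8.6%.

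**Main effect with quintile in the model.** There are now three school-level parameters. With an equal split each school has leverage 3/20, so the SE factor is √0.85 = 0.922, and the cut-off of 1.96 × 0.922 = 1.807 on 17 df gives about 8.9%. Student-level simulation gave 8.2-10.1%.

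**Interaction.** With a lower and b higher quintile schools per arm, the squared SE factor is [(a−1)/a² + (b−1)/b²] / [1/a + 1/b].

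| Schools per arm, lower:higher | SE factor | Uncorrected SE, z | Uncorrected SE, t on 16 df | Unbiased variance, t on 16 df |
|---|---|---|---|---|
| 5:5 | √(0.320/0.400) = 0.894 | 9.9% | 7.6% | 5.0% |
| 6:4 | √(0.326/0.417) = 0.885 | 10.5% | 8.2% | 5.3% |
| 7:3 | √(0.345/0.476) = 0.851 | 12.7% | 10.2% | 6.4% |

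Rates are from 400,000 replicates. Student-level GEE gave 9.3-10.7%, 9.7-11.9% and 12.5-13.9% in the third column. A t reference alone does not restore the level; the variance has to be corrected too. For the main effect, the unbiased variance with t gave 4.9-5.0%. With equal school sizes the unbiased variance used here is what the Kauermann-Carroll correction yields.

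**Model-based standard errors.** Replacing the sandwich by the model-based SE, still with z, gave 7.9-8.8% for the arm-only main effect. The problem is the small number of schools, not one choice of default.

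**The case against.** The strongest objection is that the uncorrected estimator is read into the article's silence. Nothing in Statistical methods mentions a sandwich estimator, a normal reference or the absence of a correction. A protocol article commonly leaves such details to the analysis plan, which is not shown, and the article points to Additional file 1 (Table S1) for methods of analysis, also not shown. This stands as a limit on the claim. A reader might infer that the published intervals and p values will be too optimistic; the article does not support that, because a correction may be specified elsewhere. It does not dispose of the point. The article asserts that this GEE deals with clustering, at a stated alpha and with a stated small number of schools, and both ordinary default standard errors fail to deliver that alpha.

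A reader might also take 12-13% as the error rate for the interaction. That needs about 7:3 schools per arm. The 2:1 ratio is worded in terms of participants, so an equal split of schools is equally compatible and gives about 10%. The interaction is also a subgroup analysis, not the primary test.

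Finally, correction costs precision and can overshoot. That stands for the heavier option: Mancl-DeRouen with t on 16 df rejects the interaction at only 3-4% and widens its interval by 35-50%. There is no need to use it, or to mix two estimators in one analysis.

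**Conclusion.** The point holds in conditional form. With 10 schools per arm and default GEE inference, the nominal 5% level becomes about 7-10% for the main effect, depending mainly on whether quintile is in the model, and about 10-13% for the interaction, depending on the split of schools between strata. The figures assume two-sided testing, approximately normal school means, 20 schools retained, and no correction specified elsewhere. They do not depend materially on the ICC. The issue should be settled before analysis. If the analysis plan already names a suitable correction and reference distribution, citing it closes the point.

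**What to change.** Keep the exchangeable GEE and add a sentence fixing one bias-corrected sandwich variance, for example Kauermann-Carroll, with a t reference on schools minus school-level parameters: 20 − 2 = 18 df for arm only, 20 − 3 = 17 with quintile, 20 − 4 = 16 with the interaction. The baseline score varies by student and is not counted. Apply this to every test and interval, including the subscales. Add a permutation test over the stratified school allocation as a sensitivity check for the main effect only; re-shuffling arm labels tests no effect in any school, which is not the interaction null. State the number of schools per stratum and arm.

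The design and software need not change, but the loss of precision is real:
- Main effect, arm only: (1/0.949) × 2.101/1.960 = 1.13, so intervals are about 13% wider. With quintile in the model: (1/0.922) × 2.110/1.960 = 1.17.
- Interaction: 2.120/1.960 = 1.082, divided by the SE factor, gives 1.21 (5:5), 1.22 (6:4) and 1.27 (7:3), so 21-27% wider.
- Power: at the benchmark ICC of 0.098, where the normal calculation gives 80%, a t test on 18 df gives about 75%.

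The interaction test may still run slightly above 5% (6.4% at 7:3), which should be acknowledged when it is reported.
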